### Analysis

The following analyses will be performed for each group of participants; i.e. comparing effects between interventions for those with poor and for those with strong job relations.

The rates of RTW will be compared between the two interventions at one, two and five years after randomization by means of Cox regression. The duration of sick leave will be calculated by counting the total number of weeks with sick leave during each year of follow-up. Differences between groups will be tested with the Wilcoxon rank-sum test. The WPS will be accumulated over the years and the median score will be compared between groups by means of Wilcoxon rank-sum test. Moreover, differences between interventions in frequency of participants with a WPS above 75% will be calculated using Chi^2^-test as well as the relative risk of having a score less than 75%. The percentages of participants with RTW recorded at year one, two, and five will be calculated and tested between groups by means of logistic regression.

Moreover, any other effects on health and functional capacity between interventions will be measured at the same time points and assessed by appropriate tests according to the distribution of data. Comparisons of baseline characteristics of responders and non-responders to the follow-up questionnaires will be made.

The analyses will be performed using STATA 13 IC (Stata Corp, College Station, TX), and a significance level of *p* < 0.05 will be considered statistically significant.

All analyses will primarily be performed on an intention-to-treat basis; however, per-protocol analyses will also be performed.

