## Abstract

**Background:**

Low back pain (LBP) is a common problem that affects the lives of many individuals and is a frequent cause of sickness absence. To help this group of individuals resume work, several interventions have been studied. However, not all individuals may profit from the same intervention and the effect of a given intervention on return to work (RTW) may depend on their work situation. The aim of this study is to evaluate whether employees on sick leave due to LBP and with poor job relations will benefit more from a multidisciplinary intervention, while patients with strong job relations will benefit more from a brief intervention.

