**Discussion:**

This trial will evaluate the effect of brief and multidisciplinary intervention on RTW and functional capacity among employees on sick leave due to LBP with poor or strong job relations. This will indicate whether work-related characteristics should be considered when providing treatment of LBP patients in the health care sector.

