
However, post-hoc subgroup analyses are problematic and should be verified in randomised trials. We decided to initiate a new randomised intervention study to test the findings from the previous subgroup analyses.

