### Aim

The aim of this study is to evaluate, whether employees on sick leave due to LBP and with poor job relations, will benefit more from a multidisciplinary intervention, while employees with strong job relations will benefit more from a brief intervention.

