### Hypothesis

For employees who have poor job relations i.e. feeling at risk of losing their job and/or with no perceived influence on job planning and who have not claimed additional economic compensation for their disease or injury, it is hypothesized that the multidisciplinary intervention compared to the brief intervention will:support the employees to a faster return to worksupport a sustainable RTWimprove the employees’ functional capacity

For employees who have strong job relations i.e. not feeling at risk of losing their job and with influence on job planning or who have claimed economic compensation for their disease or injury, it is hypothesized that the brief intervention compared to the multidisciplinary intervention will:support the employees to a faster return to worksupport a sustainable RTWimprove the employees’ functional capacity

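### The two group-specific comparisons are powered and tested, but the plan has no test or estimate of the difference between them, which the intended conclusion about job relations needs

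*Protocol article*

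**What the plan says.** The Abstract starts from effect modification: "the effect of a given intervention on return to work (RTW) may depend on their work situation". The Background reports an earlier trial with no overall difference but subgroup effects in opposite directions, calls post-hoc subgroup analysis problematic, and gives the reason for the new trial: "We decided to initiate a new randomised intervention study to test the findings from the previous subgroup analyses".

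The Aim is a paired statement, that employees "with poor job relations, will benefit more from a multidisciplinary intervention, while employees with strong job relations will benefit more from a brief intervention". The Hypothesis section splits it into two directional statements. For poor job relations, "it is hypothesized that the multidisciplinary intervention compared to the brief intervention will" give faster and more sustainable RTW and better function. For strong job relations, "it is hypothesized that the brief intervention compared to the multidisciplinary intervention will" do the same.

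The Power calculation sizes each group for its own HR: 0.66 in the strong group (198 employees) and 1.5 in the poor group (204), at one-sided 5% and 80% power. The Analysis section then specifies Cox regression and the other tests group by group, "comparing effects between interventions for those with poor and for those with strong job relations". No section names a model or test that compares the effect in one group with the effect in the other.

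The Abstract's Discussion states what the trial is meant to deliver: "This will indicate whether work-related characteristics should be considered when providing treatment of LBP patients in the health care sector".

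**The concern.** Treatment should depend on job relations only if the intervention effect differs between the groups. Two separate p-values do not measure that difference. One significant and one non-significant group result is compatible with the same effect in both. Two non-significant results in opposite directions are compatible with a real difference.

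The risk runs both ways. A split result may be read as proof that treatment should be matched to job relations when the effect is common to both groups. Or a real difference may be missed because neither group, or only one, reaches significance alone. In both cases the reader would have no estimate of the difference and no interval around it.

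**Working it through.** **Inputs.** From the Power calculation: HR 0.66 with N = 198 (strong), HR 1.5 with N = 204 (poor), one-sided 5%, 80% power, log-rank method. From Randomization and blinding: 1:1 allocation within each group. HRs are multidisciplinary versus brief, so values above 1 favour multidisciplinary. Two inputs are assumptions: the RTW fraction, which is not given, and the sidedness of the analysis p-value, which the Analysis section does not state. Both sidednesses are shown where it matters.

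**Step 1. The plan's own sample size.** Events = 4(1.645 + 0.842)² / (ln HR)².
- Strong: ln 0.66 = −0.4155, giving 143.2, so 144 events; 144/198 = 73%.
- Poor: ln 1.5 = 0.4055, giving 150.4, so 151 events; 151/204 = 74%.

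Freedman's formula gives 148 and 155 events (75% and 76%). The stated sizes therefore fit an RTW fraction of about 73–76%. They are consistent with the stated inputs but cannot be reproduced exactly, because that fraction is missing. Below I use 73%: 0.73 × 198 = 144.5 and 0.73 × 204 = 148.9 events.

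**Step 2. The separate tests if both planning HRs are true.** The standard error of each log HR is √(4/events): 0.166 (strong) and 0.164 (poor). The expected z values are 2.50 and 2.47.

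| | One-sided 5% | Two-sided 5% |
|---|---|---|
| Power, strong | 0.803 | 0.705 |
| Power, poor | 0.796 | 0.696 |
| Both significant (product) | 64% | 49% |
| Exactly one significant | 32% | 42% |

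Exactly one, two-sided: 0.705 × 0.304 + 0.696 × 0.295 = 0.42.

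**Step 3. The separate tests if the effect is the same in both groups.** With a common HR of 1.25, two-sided power is about 0.27 (strong) and 0.28 (poor). Exactly one is significant with probability 0.27 × 0.72 + 0.28 × 0.73 = 0.40. At a common HR of 1.2 this is 32%, and at 1.3 it is 46%.

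At 1.25 the 40% splits nearly evenly. In about 20% only the poor group is significant, favouring multidisciplinary, as hypothesised. In about 19% only the strong group is significant, also favouring multidisciplinary, which contradicts the strong-group hypothesis. Both groups significant in their hypothesised opposite directions occurs in about 0.01% of trials (0.06% one-sided).

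**Step 4. The missing contrast.** The ratio of HRs is 1.5/0.66 = 2.27, with log 0.821. Its standard error is √(4/144.5 + 4/148.9) = 0.234, so z = 0.821/0.2335 = 3.52 and two-sided power is Φ(3.52 − 1.96) = 94%. Over other RTW fractions:

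| RTW fraction | SE | z | Power, two-sided 5% |
|---|---|---|---|
| 50% | 0.282 | 2.91 | 83% |
| 73% | 0.234 | 3.52 | 94% |
| 90% | 0.210 | 3.90 | 97% |

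If only one group has an effect, power at 73% RTW drops to about 41% (HR 1.0 strong, 1.5 poor) or 43% (0.66 strong, 1.0 poor).

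**The case against.** A reader might infer that the trial's central question goes untested. The document does not support that. The Hypothesis section states two within-group directional comparisons, participants are randomised within group, each comparison has its own power calculation, and the Analysis section tests exactly those two. If both were significant in the hypothesised opposite directions, that alone would show a qualitative interaction. It is a stricter standard than an interaction test, and step 3 shows that it almost never arises falsely under a common effect. This part of the defence stands. It covers only the outcome where both succeed, which has probability 49–64% even when both planning HRs are true.

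A reader might also take the 40% in step 3 as the rate of false claims for matching. It is not. Only about half of those results resemble the hypothesis, and the plan states no rule that reads a split result as proof. The figure shows how often the planned tests leave the matter open to that reading.

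Nor does the trial simply repeat the post-hoc weakness named in the Background. The groups are prespecified, defined at baseline, randomised within and separately powered. Only the absence of a contrast carries over.

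A further temptation is to make the interaction the primary test and examine the groups only if it is significant. That would weaken the stated hypotheses: with HR 1.5 in the poor group and 1.0 in the strong group, two-sided power for the poor group would fall from 70% to about 38%. This objection also stands, and the fix below avoids the gate.

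Finally, the article is a condensed account, and a fuller plan may contain an interaction model. But the Analysis section does more than stay silent: it states that the analyses are done group by group, and that structure does not carry the conclusion announced in the Abstract.

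**Conclusion.** The point holds in this form: the plan tests the two group-specific hypotheses, but it neither tests nor estimates the difference between the group effects, on which the conclusion about matching treatment to job relations rests. When only one group is significant, that conclusion has no valid test behind it. Such a result occurs in about 42% of trials two-sided (32% one-sided) under the planning HRs, and in about 40% two-sided under a common HR of 1.25, about half of it in the hypothesised pattern.

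These figures use normal approximations for the log HR and an assumed RTW fraction of 73%, which fits the stated sample sizes. Under the planning HRs the planned 402 participants suffice for the contrast across RTW fractions of 50% to 90%. They do not suffice if only one group has an effect. In that case the interval for the ratio of HRs would often include 1, and the honest conclusion would be that a difference was not established.

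**What to change.** In the Analysis section:

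- Keep the two powered within-group Cox comparisons as they are, without making them conditional on another test.
- Add one Cox model for time to RTW on all participants (about 402), with intervention, an intervention-by-job-relations term, and the baseline hazard stratified by job-relations group. Report the ratio of HRs with its 95% confidence interval and two-sided p-value.
- State that any claim that the effect differs by job relations rests on this interaction, or on both groups being significant in opposite directions, and that one significant and one non-significant group result is not evidence of a difference.

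This should be settled before the outcome data are analysed; the Discussion expects first results in 2017. The cost is one extra model and a few sentences, with no more participants or data. The downside is a more cautious conclusion when the interaction estimate is imprecise.

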**Methods:**

The study is designed as a randomised controlled trial with up to five years of follow-up comparing brief intervention with brief intervention plus multidisciplinary intervention. Employees, aged 18–60 years, are included in the study from March 2011 to August 2016 if they have been on sick leave for 4–12 weeks due to LBP with or without radiculopathy. They are divided into two groups, a group with poor job relations and a group with strong job relations based on their answers in the baseline questionnaire. Each group is randomised 1:1 to receive the brief intervention or brief intervention plus multidisciplinary intervention. The brief intervention comprises a clinical examination and advice offered by a rheumatologist and a physiotherapist, whereas the supplementary multidisciplinary intervention comprises the assignment of a case manager who draws up a rehabilitation plan in collaboration with the participant and the multidisciplinary team.

The primary outcome is duration of sickness absence measured by register data. Secondary outcomes include sustainable RTW and questionnaire-based measures of functional capacity. Outcomes will be assessed at one, two and five years of follow-up.

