### Primary outcome

Time to RTW is the primary outcome of the study, and is defined as the period between randomisation and to RTW for at least 4 consecutive weeks without sickness absence recurrence. RTW is operationalized as not receiving any social transfer income except unemployment benefits, and will be measured by data from The Danish National Labour Market Authority’s DREAM database [32], which provides weekly information on all public transfer payments.

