### Secondary outcomes

The total number of weeks on sick leave will be measured during one, two and five years of follow-up. The same will the “Work participation score” (WPS), defined as a fraction with numbers of weeks working as the numerator and numbers of weeks receiving social transfer payments + numbers of weeks working as the denominator [33].

Furthermore, the percentages of participants with RTW recorded after one, two, and five years will also be calculated.

These outcomes will be measured with data from the DREAM database.

Pain intensity is measured by the Low Back Pain Rating scale [25], which includes three questions about pain in the lower back and three similar questions about pain in the legs. The three questions include actual pain, worst pain and average pain during the last two weeks. The pain is measured on an 11-point rating scale ranging from “no pain” (0) to “worst possible pain” (10). The sum of the answers is used for scoring (0–60).

Fear-avoidance belief is measured by three questions from the Orebro Musculoskeletal Pain Questionnaire [26]. The questions examine to what degree physical activity is believed to increase the pain, and rated from 0 (completely disagree) to 10 (completely agree), thus the sum score can range from 0 to 30.

The Roland Morris disability scale [27] is used to measure the present functional level. It includes 23 questions about the ability to perform daily activities, and is measured as “no” (0) or “yes” (1), with a sum score from 0 to 23.

Health-related quality of life is measured by Euroqol (EQ5-d) [28], which consists of five questions related to current mobility, self-care, activity, social relationship, pain and mood. It is scored on a three-point rating scale.

Self-rated health is measured by the Short Form-12 (SF-12) version 1 [29], which consists of 12 questions that correspond to eight subscales and two major summary scores, a physical component summary (PCS) and a mental component summary (MCS). The score of each major domain will be used and ranges from 0 to 100; the higher the scores, the higher the levels of functioning.

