### Power calculation

Duration of sickness absence until full RTW was chosen as the primary outcome measure and was used for sample size calculation. Data from subgroup analyses of the previous study at Silkeborg Spine Centre [13, 14, 16] showed that participants with strong job relations had a higher change of RTW when receiving the brief intervention with a hazard ratio of 0.66. In contrast, data showed that participants with poor job relations had a higher chance of RTW when receiving the multidisciplinary intervention and power calculations were based on a hazard ratio of 1.5.

A sample size calculation based on the log rank-method showed that 99 employees with strong job relations and 102 employees with poor job relations were needed in each intervention group, thus a total of 198 and 204 employees, respectively, were needed for inclusion.

The calculation was based on a one-sided significance level of 5% and a power of 80%.

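### Time to RTW is compared at one, two and five years in each group at p < 0.05, and no horizon is named as primary

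*Protocol article*

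**What the plan says.** All references are to the protocol article.

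- **Primary outcome:** "Time to RTW is the primary outcome of the study". It runs from randomisation to a return that lasts at least four consecutive weeks. No follow-up horizon is attached.
- **Analysis:** "The rates of RTW will be compared between the two interventions at one, two and five years after randomization by means of Cox regression". The section applies its analyses separately by job-relation group: "The following analyses will be performed for each group of participants; i.e. comparing effects between interventions for those with poor and for those with strong" (end of sentence omitted). The threshold is the same everywhere: "a significance level of *p* < 0.05 will be considered statistically significant". It does not say whether tests are one- or two-sided.
- **Abstract, Methods:** "Outcomes will be assessed at one, two and five years of follow-up", again without a ranking. It also says: "The primary outcome is duration of sickness absence measured by register data".
- **Secondary outcomes:** "The total number of weeks on sick leave will be measured during one, two and five years of follow-up". The Analysis section calls this count the duration of sick leave and tests it with the Wilcoxon rank-sum test.
- **Power calculation:** the primary outcome is described as duration of sickness absence up to full RTW, sized by the log-rank method. "The calculation was based on a one-sided significance level of 5% and a power of 80" per cent. The planned numbers are 198 (strong, hazard ratio 0.66) and 204 (poor, hazard ratio 1.5). No horizon or event fraction is given.

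**The concern.** The trial was set up to confirm a post-hoc subgroup finding, which the Background itself calls problematic until verified. A confirmatory test needs one designated answer per hypothesis. Here each group's hypothesis on faster RTW gets three p-values from cumulative, overlapping data, all judged at 0.05. If a group is significant at one year but not at five, or the reverse, the article does not say which result decides. A claim could then follow the favourable horizon, and the error rate would exceed the stated level.

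The outcome's name adds a smaller difficulty. A reader of the abstract alone could take the primary outcome to be total weeks of absence, which includes relapses, when the body means time to a first sustained return.

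**Working it through.** **1. The plan's own figure.** With 1:1 allocation, one-sided 5% and 80% power, the required events (Schoenfeld) are D = 4(1.645 + 0.842)² / (ln HR)².

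- HR 0.66: D = 143.2, so 144. Then 144/198 = 73% with RTW.
- HR 1.5: D = 150.4, so 151. Then 151/204 = 74% with RTW.

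Freedman's formula gives 148 and 155 events, or 75% and 76%. The planned numbers are therefore coherent with about 73-76% returning to work. The article states neither that fraction nor the time at which it applies, so the sample size does not reveal the intended primary horizon.

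**2. Inputs for the error rate.** From the article: three horizons, two groups, threshold 0.05. Assumed, because the article gives no figures: cumulative RTW of 60-80% at one year, 70-85% at two and 80-90% at five; as a slow-return stress case, 30-50%, 60-65% and 85-90%.

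**3. Method.** Under no effect, log-rank or Cox statistics on cumulative data at horizons s < t have correlation √(d_s/d_t), where d is the number of events. I drew two million triples of normal statistics with these correlations and counted how often at least one exceeded the critical value. The groups contain different people, so for per-group rate a the rate over both is 1 − (1 − a)².

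**4. Worked case, 72/80/88%.** The correlations are √(0.72/0.80) = 0.949, √(0.72/0.88) = 0.905 and √(0.80/0.88) = 0.953. At two-sided 5%, P(any |z| > 1.96) = 7.6% per group, and 1 − (1 − 0.076)² = 14.6% over both.

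**5. Range, two-sided 5%.**

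| RTW at 1/2/5 years | Per group | Either group |
|---|---|---|
| 80/85/90% | 7.0% | 13.5% |
| 70/75/80% | 7.1% | 13.7% |
| 70/78/85% | 7.5% | 14.5% |
| 60/70/80% | 8.2% | 15.6% |
| 50/65/85% (slow) | 9.2% | 17.6% |
| 40/60/90% (slow) | 10.1% | 19.2% |
| 30/60/90% (slow) | 10.7% | 20.2% |

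One-sided 5% tests over the base range give 6.8-7.8% per group and 13-15% over both. A patient-level null simulation (3,000 trials of 200 per group, log-rank at 52, 104 and 260 weeks) gave 7.4% per group and 14.3% over both.

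**6. What comes from where.** One horizon in each of two groups at 5% gives 1 − 0.95² = 9.75%. Adding the three horizons moves that to 13-16%. Within one group, the horizons move 5% to 7-8%, about 1.4 to 1.6 times nominal.

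**7. The outcome's name.** The Power calculation ties the duration wording to full RTW and to a log-rank design, which matches the Primary outcome section. The Analysis section attaches nearly the same wording to the Wilcoxon count of weeks, which the Secondary outcomes section lists as secondary. The abstract also lists sustainable RTW as secondary, although the primary definition already requires four weeks without recurrence. The terms need aligning, but the body is clear about which outcome is primary.

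**The case against.** **The article is condensed, and multiplicity rules usually sit in an analysis plan.** This stands as far as a missing multiplicity rule goes, and I do not count that as a fault. But the article does more than stay silent: it fixes three comparisons of the primary outcome per group at one threshold, with none ranked.

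**A reader might infer that the confirmatory error is about three times nominal.** The 13-16% figure is roughly that, but only when both groups form one family. The article states a separate directional hypothesis for each group, randomises each separately and sizes each separately. One overall aim does join them, so pooling can be defended, but it is a judgement. Most of the excess, up to 9.75%, comes from pooling and not from the unranked horizons.

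**A reader might also infer that the abstract names a different primary outcome, giving two routes to success.** The documents do not support this. The Power calculation bridges the two wordings, and the body lists total weeks as secondary.

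**The hypotheses are directional, so wrong-direction results should not count.** With two-sided 5% tests and the 72/80/88% case, a false positive in the hypothesised direction occurs in 3.8% per group and 7.5% over both. That is fair, but the benchmark is then 2.5% per group, so the ratio is still about 1.5. With the one-sided 5% of the Power calculation it is 7.3% and 14.1%.

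**Conclusion.** The point holds in a limited form. The primary comparison is specified at three horizons within each group at p < 0.05, and none is designated to carry the conclusion. If success may be claimed at any of them, the two-sided error per group is about 7-8% instead of 5%, or about 10% if return to work is slow. These figures rest on assumed RTW fractions and on the any-horizon reading; if one horizon was always intended, the inflation disappears once it is named. The trial-wide 13-16% should be quoted only with the caveat on pooling. The abstract's wording is an ambiguity to tidy. The inflation is moderate, but a disagreement between horizons would leave the trial without a defined answer.

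**What to change.** In the Analysis section, state that the primary analysis in each group is time to RTW, as defined under Primary outcome, at one named horizon. This could be censoring at 52 weeks, or the horizon behind the sample size if that was different. Label the other two Cox analyses secondary. Reword the abstract to time to RTW, so that it agrees with the Primary outcome and Power calculation sections, and keep the duration wording for the total-weeks outcome only.

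This restores 5% per group. The cost is a few sentences, and the other two horizons lose confirmatory status.

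I would not add an intervention-by-group interaction test as a gate. With 144 and 151 events the standard error of the difference in log hazard ratios is √(4/144 + 4/151) = 0.233. Two-sided power at 5% is about 94% if both opposite effects are real (0.821/0.233 = 3.52), but about 41% if only the hazard ratio of 1.5 is (0.405/0.233 = 1.74). That is a change of decision rule, and it is not needed to settle the horizon.
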